#### Outcome measures

Outcome measures will include fluid biomarkers in blood and saliva, visual functions tests, social and occupational functioning assessments, and self-reported quality of life outcomes such as Brain Injury Vision Symptom Survey visual impairment, Patient Health Questionnaire-9, General Anxiety Disorder-7, Post-Traumatic Stress Disorder Checklist for DSM-5, Suicidal Behaviour Questionnaire Revised, Alcohol Use Disorders Identification Test and EuroQol 5-Dimension 5-Level (Quality of Life) (tables4^7^).

**Table 4 T4:** Potential fluid biomarkers

Biomarker	Description	Reference
Glial fibrillar acidic protein (GFAP)	Astroglial injury marker	37 40
S100β	Astroglial injury marker	^37 38 41^
Neuron-specific enolase (NSE)	Neuronal injury marker	^42 43^
Neurofilament light chain (NF-L)	Neuronal injury marker	^37 39 40^
Ubiquitin C-terminal hydrolase-L1 (UCLH-1)	Neuronal injury marker	^37 39 40^
Phosphorylated tau (pTau)	Neuronal injury marker	^37 39 40^
Myelin basic protein (MBP)	Neuronal injury marker, myelin disruption	^44 45^
Tumour necrosis factor-α (TNF-α), interleukin-6 (IL-6) and IL1-β	Inflammation	^45^
Cortisol	Stress response protein	^46^

**Table 5 T5:** miRNA biomarkers

Biomarker	Description	Reference
miR-20a-5p	Neuronal injury marker	^47^
miR-24-3 p	Neuronal injury marker	47 49
miR-27b-3p	Recovery process monitoring	^48^
miR-29c-3p	Correlate with burden of head impacts and neuronal development overtime since injury	^50 51^
miR-181a-5p	Associated with protein modifications in traumatic brain injury	^48 52^

**Table 6 T6:** Visual function assessments

Test used	Visual function assessed	References
Acuity Plus package on the Colour Assessment and Diagnosis machine (CAD; City Occupational, London, UK)	Visual acuity, colour vision and contrast	^20^
Humphrey visual field testing using the 24-2 SITA-Fast technique (Carl Zeiss, Cambridge, UK)	Visual field	^20 53^
Email package on the CAD	Saccadic latency	^20 54^
Autorefraction (Rexxam, Tokyo, Japan)	Accommodation	^20 54^
Pupillometry (DP-2000, Neuro-optics California, USA)	Pupillary reactions	2055 57
Optic coherence tomography (OCT; Heidelberg Spectralis, Heidelberg Engineering, Heidelberg, Germany) using Posterior Pole, retinal nerve fibre layer, and disc volume images	Retinal thickness	^58^
OCT angiography (OCTA), HS-20 scanning protocol.	Retinal blood flow	^58^

**Table 7 T7:** Patient-reported outcomes assessed and scales

Outcome assessed	Scale used	Reference
Brain injury-induced vision symptoms	BIVSS (Brain Injury Vision Symptom Survey)	^59^
Depression	PHQ-9 (Patient Health Questionnaire)	^60^
Anxiety	GAD-7 (General Anxiety Disorder)	^61^
Post-traumatic stress disorder (PTSD)	PCL-5 (Checklist for DSM-5)	^62^
Suicide ideation	SBQ-R (Suicidal Behaviour Questionnaire Revised)	^63^
Alcohol abuse	AUDIT (Alcohol Use Disorders Identification Test)	^64 65^
Quality of life	EQ-5D-5L (Quality of Life)	^64 65^

#### Fluid biomarkers

Fluid biomarkers from blood will look for a panel of biomarkers, summarised in table 4, that detect ongoing astroglial and neuronal injury/damage such as GFAP and neuron-specific enolase. Salivary biomarkers will look for dysregulated micro RNAs after TBI, including miR20a-5p and miR-24-3p (table 5).

#### Visual function tests

Visual function tests are summarised in table 6.

#### Mental health and quality of life outcome measures

Quality of life outcomes such as visual impairment, depression, anxiety, PTSD, suicide ideation, alcohol use disorder and alcohol abuse and overall quality of life symptoms will be assessed using validated questionnaires, summarised in table 7.

In addition, clinician-led social occupation and functioning (SOFAS) test will be conducted at each face-to-face visit,^32^ while head injury outcomes using the Glasgow Coma Scale^33 34^ and the Mayo-Portland Adaptability Inventory^35^ will be assessed at the final visit as part of routine care by a physician.

#### Statistical methods

Analyses will include all available data of recruited patients (not restricted to patients with complete follow-up). Between group comparisons will evaluate susceptibility to poor mental health and quality of life outcomes. Longitudinal data may show the latency of onset of mental health and quality of life problems after acute TBI, in order to time future interventions.

Candidate serum and visual biomarkers will be compared between groups and associated with mental health and quality of life outcomes to look for predictive value. Many of these data are continuous and normally distributed and repeated measures data (including data from both right and left eyes). As such, generalised estimating equations will be used to determine changes over time with data from each eye and different time points treated as repeated measures, with a binomial distribution used for binary and ordinal outcomes as appropriate. Trial statisticians in the Birmingham Clinical Trials Team will be engaged for further statistical advice, if required.

This is a pilot study to evaluate longitudinal changes in fluid and visual biomarkers of brain injury, mental health status and self-reported quality of life measures in patients with TBI (civilian and military veterans). As such, sample size is based on:

Statistical advice that in a pilot/feasibility study, 30 subjects in each group are recommended to allow estimation of the parameters of interest.Childs *et al*^36^ who showed a difference of 5 µm in global retinal nerve fibre layer (RNFL) thickness between boxers and controls, an average RNFL thickness of 101 and an SE of 1.8.

Past experience in the concussion clinic suggests that we can follow 80% of patients at the 3-month point (ie, only 20% lost to follow-up). We powered the study to detect a 5 µm change in the RNFL thickness, assuming a correlation of 0.9 between repeated measures (conservative given that in the absence of pathology, RNFL thickness varies very little). Simulated power calculations in R revealed that 24 participants with complete data (recruiting 30 and assuming a 20% drop out) would have >80% power to detect a 2 µm change in RNFL thickness and 100% power to detect a 5 µm decrease.

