**Figure 1 F1:**
[figure not shown]
Biofluids, visual, psychiatric assessments and PROMs timeline. PROMs, patient-reported outcome measures; TBI, traumatic brain injury.

In the acute TBI group (predictive group), biofluid collection, visual function, depression, anxiety, PTSD, suicidal behaviour, alcohol use and quality of life data through patient-reported outcome measures (PROMs) will be collected within 14 days after TBI. The same tests will be repeated in outpatients at 6- and 12 months after enrolment. At 1 month after enrolment, biofluid collection, psychiatric symptoms and quality of life outcomes will be repeated to monitor the recovery trajectory. PROMs will be completed remotely by each participant every 3 months for the 12-month follow-up period.

Veterans will also have biofluids collected, visual function and psychiatric assessments and quality of life measures collected using PROMs at enrolment and at 6- and 12-month follow-up. PROMs will also be completed remotely by participants every 3 months.

Control participants will be age and gender-matched to the acute TBI group and recruited from both civilian and veterans cohorts with no TBI history. They will have biofluids collected, visual function and psychiatric assessments and quality of life measures collected via PROMs at enrolment and at 6 months only (see tables1^3^ for planned assessment schedules in the three participant groups).

**Table 1 T1:** Assessments delivered within the trial period for acute traumatic brain injury patient group

	Trial period			
	Enrolment	Initial assessment (may be at enrolment)	Postallocation (monitoring interval clinically determined)	Close-out
Timepoint	−t_1_	Contact 1 (0–14 days post head injury or at enrolment)	Contact 2–5 (1, 3, 6 and 9 months after head injury or enrolment)	Contact 6 (12 months after head injury)
Enrolment				
Eligibility screen	X			
Informed consent	X			
Assessments				
Collect blood and saliva		X(face to face)	X(1 and 6 months only, face to face)	X(face to face)
Visual function tests (visual acuity, visual field, optical coherence tomography (OCT), OCT angiography, pupillometry, saccadic latency, autorefraction, colour vision and contrast sensitivity)		X(face to face)	X(1 and 6 months only, face to face)	X(face to face)
Social and occupational functioning assessment		X(face to face)	X(1 and 6 months only, face to face)	X(face to face)

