### Consent

Within both veteran and control groups, participants should have capacity to consent and be willing and able to follow the protocol, except for the acute TBI cohort, who may not have capacity to consent as a result of TBI. Written consent will be obtained by the local research team, which may include the site principal investigator, co-investigators or research assistants. Veterans will be recruited through veteran charities such as Bravo Victor, Blind Veterans UK or other veterans charities and organisations. In the acute TBI groups attending the QEH in Birmingham for head injury, identified participants may not have the capacity to consent and as such, written consultation will be obtained from a personal (ie, relative) or nominated (professional) consultee. However, if a patient regains consciousness and capacity, their consultee will be notified, and the patient will be given the opportunity to provide written consent to remain in the study or withdraw. Unconscious patients will only have blood collected and OCT scans conducted as all other tests require a patient to be conscious and have capacity to complete. The willingness of participants to remain in the study will be re-affirmed at each study visit with the patient or consultee as appropriate. Patients have the right to withdraw from the study at any time, but all data collected will be retained and used in the analysis to avoid bias in assessment of outcomes.

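### All-available-data GEE meets missingness that depends on injury state in the acute group: early mental-health and quality-of-life estimates, and the recovery trajectory, may be biased

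*Protocol article*

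**What the plan says.** Three parts of the protocol article bear on this.

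- **Consent.** In the acute group "identified participants may not have the capacity to consent and as such, written consultation will be obtained" from a consultee. The section then says "Unconscious patients will only have blood collected and OCT scans conducted as all other tests require a patient to be conscious and have capacity". The explicit restriction is for unconscious patients, but the reason given also covers conscious patients who lack capacity. Recovery is foreseen: "if a patient regains consciousness and capacity, their consultee will be notified", and the patient may then stay in or withdraw.
- **Overall study design and Table 1.** For the acute group, biofluids, visual function, psychiatric measures and patient-reported outcomes (PROMs) "will be collected within 14 days after TBI". Table 1 lists them all at contact 1 without exception. On later visits the text says "The same tests will be repeated in outpatients at 6- and 12 months after enrolment"; PROMs also recur at 1, 3 and 9 months.
- **Statistical methods.** "Analyses will include all available data of recruited patients (not restricted to patients with complete follow-up". For repeated measures, "generalised estimating equations will be used to determine changes over time with data from each eye and different time points treated as repeated measures". These data are to serve group comparisons of mental health and quality of life, and to describe when problems begin after acute TBI.

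Study limitations names missed visits, withdrawal and the veterans' varying time since injury. It does not mention assessments that cannot be done because of the patient's state.

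**The concern.** Unweighted GEE on available data is generally valid only if data are missing completely at random, or if missingness depends only on covariates in the model. The Consent rule breaks the first condition by design, and no covariate is named that would meet the second. The patients without PROMs at the first contact are those in the worst neurological state at that time.

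Two aims are exposed. Early acute-group means, and their contrast with controls, describe only the patients who could be assessed. In addition, patients who recover enter the PROM series late, so the average can move over time because its membership changes. That matters for latency of onset, which the article wants in order to time future interventions.

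**Working it through.** **1. The plan's own missing-data figure.** 24 complete participants at 20% dropout: 24/(1 − 0.20) = 30. This reproduces. It concerns RNFL thickness, which OCT still measures in unconscious patients, so the present point does not touch it. The 20% is an overall 3-month loss from a concussion clinic and is not tied to patient state.

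**2. Schedule against rule, acute group, first contact.**

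| Assessment | Table 1 | Consent section, if unconscious |
|---|---|---|
| Blood | scheduled | collected |
| OCT | scheduled | done |
| Saliva | scheduled | not collected |
| Functional vision tests | scheduled | not done |
| Social and occupational functioning (SOFAS) | scheduled | not done |
| PROMs | scheduled | not done |

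**3. Size of bias.** With a separate mean per contact and independence working correlation, GEE returns the mean of those observed. Let p be the share unassessable at first contact, d their mean score minus that of the others (higher = worse), and r the fraction of them assessable at a later contact. Their share among those observed is q = pr/(pr + 1 − p), and bias = d(q − p). At first contact r = 0, so bias = −p·d.

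Assumptions, none from the documents: p = 10%, 30% or 50%; d = 3 points; SD 6; r = 0.5, 0.8 and 0.9 at 1, 6 and 12 months.

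Example, p = 30%:
- First contact: −0.30 × 3 = −0.90.
- 12 months: q = 0.27/(0.27 + 0.70) = 0.278; bias = 3 × (0.278 − 0.300) = −0.06.
- Change from 0 to 12 months: −0.06 − (−0.90) = +0.84, an apparent worsening produced by case mix alone.

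A simulated GEE (one data set of 3,000 patients per row, within-patient correlation 0.6) agrees for independence and shows how far an exchangeable structure helps. Cells give bias at first contact / at 12 months / in the change:

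| p | Formula | Simulated, independence | Simulated, exchangeable |
|---|---|---|---|
| 10% | −0.30 / −0.03 / +0.27 | −0.27 / −0.02 / +0.25 | −0.09 / −0.02 / +0.07 |
| 30% | −0.90 / −0.06 / +0.84 | −0.81 / −0.02 / +0.79 | −0.23 / −0.02 / +0.21 |
| 50% | −1.50 / −0.08 / +1.42 | −1.55 / −0.08 / +1.48 | −0.35 / −0.08 / +0.27 |

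**4. Other assumptions.**
- No recovery: bias stays near −p·d at every contact, and the change is little affected.
- d = 0: no bias (simulated values lie within 0.09 of zero, which is noise).
- d = −3: the sign reverses. Independence first-contact bias is +0.30, +0.96 and +1.45, and bias in the change is −0.27, −0.85 and −1.36.

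**5. Against sampling error.** At p = 30%, 21 acute patients face 30 controls: SE = 6 × √(1/21 + 1/30) = 1.71 points, so a bias of 0.90 is about 0.53 SE. At p = 10% (27 v 30) it is 0.30/1.59 = 0.19 SE, and at p = 50% (15 v 30) it is 1.50/1.90 = 0.79 SE.

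**The case against.** **The analysis plan may deal with this.** An article condenses its statistics. Imputation, weighting and sensitivity analyses normally sit in an analysis plan, which is not shown, and nothing in Statistical methods forbids covariates. Keeping all available data is also better than restricting to completers. This stands as far as it goes: the absence of a missing-data method is not the finding. The finding is that a stated analysis, a stated assessment rule and a stated schedule do not fit together.

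**A reader might infer that acute-group burden will be underestimated throughout.** The documents do not support that. They give neither the share unconscious nor any statement that these patients later report worse depression, anxiety, PTSD or quality of life. A single-contact illustration can look striking. If 40% are severe and 1 SD worse, with PROMs observed in 40% of them and 90% of the others, the severe share among those observed is 0.16/0.70 = 0.229. The estimate is then 0.23 SD against a true 0.40 SD, 43% too small. Every input is assumed, however, and the illustration contains neither repeated contacts nor recovery.

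**A reader might also infer that biomarker–outcome links are pulled towards zero.** That has not been calculated. Selection on severity can lower a correlation, but it need not bias the slope of a correctly specified regression.

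**Weighting has its own flaw.** A patient unconscious at a contact has no chance of giving a PROM there, so weighting on capacity violates positivity. Imputing a self-report for that patient has no observed counterpart to draw on. With 30 acute patients, many auxiliary variables would be unstable. All of this stands and limits the remedy.

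**Conclusion.** The point holds as a conflict between the stated analysis and the design. Followed as written, missing PROM, saliva, SOFAS and functional vision data depend on neurological state, and plain GEE does not account for it. First-contact acute-group estimates may be biased. The likely direction is towards less burden, least certainly so for self-reported depression, anxiety and PTSD. The 0–12 month trajectory and latency of onset may be distorted as patients recover and join the series.

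Under the assumptions shown, first-contact bias is 0.3 to 1.5 points on an SD of 6 (0.05 to 0.25 SD) with independence GEE and 0.09 to 0.35 points with exchangeable GEE. Each is below one SE of the group difference. By 12 months it is under 0.1 point if 90% recover; without recovery it persists. Blood markers and OCT, including the RNFL measure behind the sample size, are not affected. For a pilot meant to inform a larger study this should be corrected, but it does not invalidate the design.

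**What to change.** 1. Reconcile Table 1 with the Consent section, so that schedule and rule agree on what is collected from acute patients who are unconscious or lack capacity.
2. Record and report, by contact, the share of each assessment missing and why: unconscious, no capacity, died, declined.
3. Define first-contact PROM results as applying to assessable patients only.
4. For change over time and for later group comparisons, adjust for injury severity at entry. Controls have no severity value, so fit severity levels within the acute group and average over the enrolled mix. Alternatively, use multiple imputation with severity and one or two baseline blood or OCT measures, only for patients who were able to respond but have missing data. Both options assume that severity is recorded at entry. The moderate-severe entry definition implies this, but the article does not state it.
5. Repeat the trajectory analysis in patients assessable from the first contact, so that case mix is held constant.
6. Add one delta-shift sensitivity analysis, run in both directions because the sign is unknown.
7. Do not weight on capacity status, and do not impute self-reports for patients unconscious at that contact.

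The cost is analysis wording, one reason-for-missing field, modest extra programming and somewhat wider intervals. In the restricted trajectory analysis, 27, 21 or 15 of 30 acute patients would remain at p = 10%, 30% or 50%. The SE of an acute-group mean then rises by √(30/27) = 1.05, √(30/21) = 1.20 or √(30/15) = 1.41 times, relative to all 30 being observed.

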### Study hypotheses

TBI-induced alterations in brain structure are associated with the risk of subsequent mental health disorder.TBI-induced changes can be detected using fluid and imaging biomarkers.TBI-induced changes in biomarkers may identify those at risk of poor recovery and the development of mental health conditions affecting the quality of life.Changes in visual structure and function predict mental health and quality of life and associate with TBI-related biomarkers.

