### Methods and analysis

#### Overall study design

This is a single centre prospective observational pilot study in three groups of 30 participants each: civilians admitted to the Queen Elizabeth Hospital (QEH) in Birmingham with acute moderate-severe TBI, military veterans with diagnosis of a previous TBI and a control group of civilians or veterans with no history of TBI. Patients will undergo visual, biochemical and mental health assessments, as well as patient-reported symptoms and quality of life outcome measures over the course of a 1-year follow-up period (see figure 1 for overview).

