Self-reported outcomes measures collected by post or electronically (eg, BIVSS visual impairment, PHQ-9, GAD-7, PCL-5, SBQ-R, AUDIT and EQ-5D-5L)		X(all collected remotely)	X(1, 3, 6 and 9 months, all collected remotely)	X(all collected remotely)
Head injury outcome				X

AUDITAlcohol Use Disorders Identification TestBIVSSBrain Injury Vision Symptom SurveyEQ-5D-5LEuroQol 5-Dimension 5-Level (Quality of Life)GAD-7General Anxiety Disorder-7PCL-5Post-Traumatic Stress Disorder Checklist for DSM-5PHQ-9Patient Health Questionnaire-9SBQ-RSuicidal Behaviour Questionnaire Revised

**Table 2 T2:** Assessments delivered within the trial period for the veteran’s participant group

	Trial period			
	Enrolment	Initial assessment (may be at enrolment)	Postallocation (monitoring interval clinically determined)	Close-out
Timepoint	−t_1_	Contact 1 (at enrolment)	Contact 2–4 (3, 6 and 9 months after enrolment)	Contact 5 (12 months after head injury)
Enrolment				
Eligibility screen	X			
Informed consent	X			
Assessments				
Collect blood and saliva		X(face to face)	X(at 6 months only, face to face)	X(face to face)
Visual function tests (visual acuity, visual field, optical coherence tomography (OCT), OCT angiography, pupillometry, saccadic latency, autorefraction, colour vision and contrast sensitivity)		X(face to face)	X(at 6 months only, face to face)	X(face to face)
Social and occupational functioning assessment		X(face to face)	X(at 6 months only, face to face)	X(face to face)
Self-reported outcomes measures collected by post or electronically (BIVSS visual impairment, PHQ-9, GAD-7, PLC-5, SBQ-R, AUDIT and EQ-5D-5L)		X(all collected remotely)	X(at 3, 6 and 9 months, all collected remotely)	X(all collected remotely)
Head injury outcome				X

AUDITAlcohol Use Disorders Identification TestBIVSSBrain Injury Vision Symptom SurveyEQ-5D-5LEuroQol 5-Dimension 5-Level (Quality of Life)GAD-7General Anxiety Disorder-7PCL-5Post-Traumatic Stress Disorder Checklist for DSM-5PHQ-9Patient Health Questionnaire-9SBQ-RSuicidal Behaviour Questionnaire Revised

**Table 3 T3:** Assessments delivered within the trial period for healthy control group

	Trial period	
	Initial assessment (may be at enrolment)	Postallocation (monitoring interval clinically determined)
Timepoint	Contact 1 (single assessment point)	Contact 2 (6 months after enrolment)
Enrolment		
Eligibility screen	X	
Informed consent	X	
Assessments		
Collect blood and saliva	X(face to face)	X(face to face)

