#### Eligibility and exclusion criteria

To be included in the study, participants are required to be over 18 years old, have two eyes and must have sustained TBI. Control participants should not have a diagnosis or history of moderate or severe TBI. Exclusion criteria for all three groups include: participants below 18 years old, are pregnant, have pre-existing neuropsychiatric conditions, retinal or optic nerve disorder or are registered as sight impaired.

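### In the 0–14 day acute-versus-control comparison, TBI coincides with hospitalised trauma, so early differences in the inflammation and stress markers cannot be called TBI-induced

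*Protocol article*

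**What the plan says.** All references are to the protocol article.

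- **Acute group.** Overall study design defines it as "civilians admitted to the Queen Elizabeth Hospital (QEH) in Birmingham with acute moderate-severe TBI". The same section says that biofluids, visual tests and questionnaires "will be collected within 14 days after TBI"; Table 1 gives contact 1 as 0–14 days.
- **Comparator.** "Control participants will be age and gender-matched to the acute TBI group". The title of Table 3 reads "Assessments delivered within the trial period for healthy control group". Controls are measured at enrolment and at 6 months.
- **Eligibility.** The one condition specific to controls is "Control participants should not have a diagnosis or history of moderate or severe TBI". The exclusions for all groups do not restrict extracranial injury.
- **Hypothesis.** "TBI-induced changes can be detected using fluid and imaging biomarkers".
- **Analysis.** Statistical methods states "Candidate serum and visual biomarkers will be compared between groups" and adds that the markers will be related to mental health and quality of life to look for predictive value.
- **Markers.** Table 4 lists TNF-α, IL-6 and IL1-β under inflammation and cortisol as "Stress response protein". It describes the other seven (GFAP, S100β, NSE, NF-L, UCLH-1, pTau, MBP) as astroglial or neuronal injury markers.

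**The concern.** The second hypothesis is causal, and a causal reading of a group difference needs the groups to differ in TBI and in little else that moves the marker. In the first two weeks they do not. Acute patients are admitted trauma patients, some of whom may have injuries outside the head, and controls are healthy people. A marker described only as inflammation or stress response could rise from either source.

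The analysis within the acute group has a related weakness. Total injury burden could raise such a marker and, by another route, worsen later quality of life, which would make the marker look predictive.

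The pilot is meant to inform a larger study, so the risk is that non-specific markers are carried forward as markers of TBI. Study limitations names only the varying time since injury in veterans as a confounder.

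**Working it through.** **What coincides with TBI in the early comparison**

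| | Acute, 0–14 days | Control, enrolment |
|---|---|---|
| TBI | yes, moderate-severe | no |
| Hospital admission for trauma | yes, all | no (labelled healthy) |
| Extracranial injury | possible, not restricted | not expected |
| Matched factors | age, gender | age, gender |

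The first two rows are fully aliased. Adjustment across groups cannot separate them, because the exposure is essentially confined to one arm. A covariate list in an unseen analysis plan would not change this, since it cannot supply a comparator.

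**Markers affected.** By Table 4's own descriptions: 3 (inflammation) + 1 (stress response) = 4 of 11.

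**Sample size.** The plan's figure reproduces: 24 / (1 − 0.20) = 30 per group. The stated power concerns change in RNFL thickness and does not address this comparison.

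**Illustrative size.** The documents give no extracranial-injury rate and no effect of such injury on any marker, so both inputs are assumptions.

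- q = share of acute patients with relevant extracranial injury: 0.30 to 0.60
- d = shift in the marker among them: 0.5 to 1.0 SD
- True TBI effect: zero
- Shift in the group mean = q × d: 0.30 × 0.5 = 0.15 SD, to 0.60 × 1.0 = 0.60 SD
- Standard error of a difference, 30 per group: √(1/30 + 1/30) = 0.258 SD
- Ratio: 0.15 / 0.258 = 0.6, to 0.60 / 0.258 = 2.3
- Chance of a nominally significant result (two-sided 5%, normal approximation) = Φ(ratio − 1.96) + Φ(−ratio − 1.96): about 9% to 64%

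An intermediate case, q = 0.40 and d = 1.0, gives a shift of 0.40 SD and a chance of 34% with 30 per group, or 28% with 24. At the middle of both ranges (0.45 × 0.75 = 0.34 SD) the ratio is 1.3, below 1.96. Only the upper part of the range crosses conventional significance.

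**Cost of the isolated-TBI subset, same q.** 30 × (1 − q) = 21 down to 12 acute patients before dropout. Against 30 controls the standard error becomes √(1/21 + 1/30) = 0.285, up to √(1/12 + 1/30) = 0.342 SD.

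**The case against.** The strongest reply has four parts.

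1. **No early test is named.** Statistical methods does not designate an acute-versus-control contrast at contact 1 as the test of the second hypothesis, and most of the section concerns change over time. This is true. Still, both groups are measured at enrolment, the between-group sentence covers that comparison, and the article presents early capture as a strength. The point is about what such a difference could support.

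2. **Covariates and recorded fields belong in the full protocol or analysis plan.** This stands. Their absence from the article is not held against it. The choice of comparator and the causal wording are fixed in the article.

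3. **The scope is limited.** A reader might infer that all early biomarkers and visual tests are compromised. The documents do not support that. Seven of eleven blood markers are described as neuronal or astroglial, and RNFL thickness, used for the power statement, is not implicated. A reader might also extend the point to pupillometry and saccadic latency through hospital drugs. That is secondary at most: under Consent, unconscious patients have only blood and OCT, and the article says nothing about drug effects on these tests. That controls are uninjured is itself inferred from the word healthy.

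4. **Parts of the design are less exposed.** Acute patients and controls are both measured at 6 months, and veterans with previous TBI give a contrast with controls outside the acute phase. Both help with the hypothesis, but neither repairs the early comparison.

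**Conclusion.** The concern holds in a limited form. For TNF-α, IL-6, IL1-β and cortisol, an acute-versus-control difference in the first 14 days cannot be attributed to TBI as distinct from hospitalised trauma, so it cannot support the TBI-induced wording of the second hypothesis. This rests on the admitted acute group, the healthy comparator and the Table 4 descriptions.

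The size cannot be determined from the documents; the 0.15 to 0.60 SD is wholly assumed. A reader might infer that the early comparison will come out positive whatever TBI does. That is not supported: most of the assumed range lies below the significance threshold. The pilot's 6-month, 12-month and veteran comparisons are less exposed.

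**What to change.** - Take extracranial injury severity for the acute group from the existing hospital record, and include it as a covariate in the within-acute models that relate markers to outcomes.
- Repeat the early acute-versus-control comparison in patients with isolated TBI, as a sensitivity analysis. This addresses extracranial injury but not admission itself.
- Report early differences in the four non-specific markers as associated with acute hospitalised trauma including TBI.
- Show the already scheduled 6-month acute-versus-control contrast beside the early one. It should not replace it, since the early window is a main reason for having the acute cohort.
- Record surgery and drug exposure descriptively only. They may be consequences of TBI severity, so adjusting for them or restricting on them could remove real TBI effect.
- Add extracranial injury to Study limitations.

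The cost is a few fields of record abstraction, a more modest early claim and a smaller, less precise isolated-TBI subset. No new group or visit is needed.
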